### Quantitative sample size

Sample size was calculated for the primary endpoint (22 weeks) for older adults and family caregivers separately and the largest sample size was selected. The sample size for the primary caregiver outcome measure (CATOM) was chosen to detect a 10 % decrease in perceived burden. This is consistent with the caregiver burden change noted in a prior trial using CATOM scores at baseline and after 16 weeks [31]. It indicates a one-level decrease on half of the items for the family caregivers (nearly always → frequently → sometimes → rarely → not at all). The primary older adults’ outcome measure is the SMAF. The sample size was chosen in order to detect an improvement of 9 % following the intervention. This value is intermediate between the minimal detectable difference and the change measured by administering the SMAF in a study examining the impact of a rehabilitation program on individuals with post-cerebral vascular accident [44, 45].

To determine an effect size, Cohen’s *D* was calculated using standard deviations from our prior study [31] and then transformed into Cohen’s *F* [46, 47]. As the effect size was smaller for the SMAF, we used this value to simulate various potential scenarios using G*Power 3.1.0.87. For these simulations we varied several variables including 1) effect size (0.13 to 0.15), 2) correlations among repeated measures (which previous data suggest will be moderate for pre-post intervention and strong between post intervention and long term follow up, e.g. 0.5 to 0.6), and 3) violations of sphericity (due to differences in variances over time, e.g., 0.6 to 0.9). The average of these sample sizes is 102. Based on approximately a 20 % dropout rate for the main trial endpoint (suggested by the prior study in which dropout occurred exclusively due to health related issues, which are common in this population), a sample of 120 dyads will be recruited (40 from each site).

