**Methods/design:**

This research will use a combination of quantitative and qualitative methods. The quantitative portion will be an experimental, single-blinded study in which participants are randomly assigned to either an experimental assistive technology intervention or a standard care group. We will enroll 240 participants (120 dyads) into the study from three Canadian sites. Participants will include older adults (>55) and family caregivers who provide ≥4 h per week of assistance with daily activities and social participation. The primary outcome measure for the older adults will be the Functional Autonomy Measurement System, and the primary outcome measure for the caregivers will be the Caregiver Assistive Technology Outcomes Measure. Qualitative data will be collected through detailed records of the therapists’ interventions, as well as through interviews with dyads and therapists following the interventions. Data collection will occur at baseline (T_0_) with follow-ups at 6 weeks (T_1_), 22 weeks (T_2_), and 58 weeks (T_3_) after baseline evaluation.

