### Quantitative study design

This study protocol follows CONSORT guidelines. A single blind RCT will be conducted with 120 dyads, each consisting of an older AT user and his or her principal family caregiver. Both the experimental and customary care interventions will be provided to participants after the administration of the outcome measures at baseline. The measures will be re-administered to both groups 6 weeks, 22 weeks (the main trial endpoint), and 58 weeks after baseline evaluation. Figure 1 depicts the study design.

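### The planned 120 dyads leave about 96, not 102, at 22 weeks if dropout is the stated 20%

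*Protocol article*

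**What the plan says.** The section headed Quantitative sample size takes the smaller of two effect sizes, that for the SMAF, and runs G*Power over three ranges:

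- "effect size (0.13 to 0.15" for the effect, as Cohen's f;
- 0.5 to 0.6 for the correlation among repeated measures;
- 0.6 to 0.9 for the sphericity correction.

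It then reports: "The average of these sample sizes is 102". The next sentence opens "Based on approximately a 20 % dropout rate for the main trial endpoint", credits that rate to the group's prior study, and ends with the recruitment target: "a sample of 120 dyads will be recruited (40 from each site".

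The unit is clear. The Abstract says "We will enroll 240 participants (120 dyads) into the study from three Canadian sites", and Quantitative study design repeats 120 dyads and identifies "22 weeks (the main trial endpoint". The SMAF is scored once per older adult, so one dyad supplies one observation unit and 102 is a number of dyads.

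**The concern.** The section presents 120 as the result of enlarging 102 for 20% dropout. Three printed figures are therefore tied together, and any two of them fix the third. They do not agree, and the disagreement runs in the unfavourable direction: if dropout is what the authors expect, the trial reaches its main endpoint with fewer dyads than the average it was sized on. A reader who takes the sentence at face value will believe that the 20% loss has been fully absorbed.

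**Working it through.** **Inputs.** From Quantitative sample size: 102 (average required), 20% (dropout at 22 weeks), 120 (recruited, 3 × 40). The Abstract's 240 participants = 2 × 120, so the unit is consistent.

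**Trying to reproduce 120.**

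- Standard inflation, N/(1 − d): 102/(1 − 0.20) = 127.5, rounded up to 128. Not 120.
- The common mistaken inflation, N × (1 + d): 102 × 1.20 = 122.4. This is closer to 120 but still above it. The target may be this figure rounded down to 40 per site, but the article does not say so.
- Dropout at which 120 is exact: 1 − 102/120 = 0.15.

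**What 120 delivers.** 120 × (1 − 0.20) = 96. The shortfall is 102 − 96 = 6 dyads, and 6/102 = 5.9%. With equal site numbers, 128 becomes 129 (43 per site).

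**Room in the word approximately.** Recruitment needed to keep 102:

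| Dropout | 102/(1 − d), rounded up | Left from 120 |
|---|---|---|
| 15% | 120 | 102.0 |
| 17% | 123 | 99.6 |
| 18% | 125 | 98.4 |
| 19% | 126 | 97.2 |
| 20% | 128 | 96.0 |
| 22% | 131 | 93.6 |

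**What six dyads cost in power.** The section states no alpha, target power, test or number of measurements, so this step is illustrative. Assumptions: alpha 0.05, two equal groups, group-by-time interaction in a repeated measures analysis of variance with m visits. Then

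- noncentrality λ = f² × N × m × ε / (1 − ρ);
- numerator df = (m − 1)ε; denominator df = (N − 2)(m − 1)ε.

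The grid is the eight corners of the stated ranges: f = 0.13 or 0.15, ρ = 0.5 or 0.6, ε = 0.6 or 0.9. For the least favourable corner with three visits and N = 96, λ = 0.0169 × 96 × 3 × 0.6/0.5 = 5.84, and power is 0.641.

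| Visits | N | Mean power | Lowest | Highest |
|---|---|---|---|---|
| 3 (to 22 weeks) | 102 | 0.828 | 0.669 | 0.953 |
| 3 | 96 | 0.805 | 0.641 | 0.940 |
| 4 (to 58 weeks) | 102 | 0.885 | 0.741 | 0.980 |
| 4 | 96 | 0.865 | 0.713 | 0.973 |

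Mean power falls by 2.3 points with three visits and 2.0 with four. Because λ depends on f²N, holding power fixed needs f to rise by about √(102/96) = 1.031, so the detectable effect grows by about 3%.

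**Can 102 itself be reproduced?** Not firmly. Under the same assumptions the average required size at 80% power is about 95 to 97 (three visits) or 81 to 82 (four visits); at 90% power with four visits it is about 106 to 107. The dropout arithmetic does not depend on this, since it takes 102 as printed.

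**The case against.** The best defence concerns size. The 102 is the mean of a set of scenarios and not a threshold: with three visits and 80% power, individual scenario sizes run from 64 to 138 under the assumptions above, and six dyads are small beside that spread. Mean power at 96 also stays at or above about 80% in both versions of the calculation. The low power in the worst corner comes mainly from averaging over scenarios, since that corner is under 80% even at 102; the dropout slip adds only about 3 points. All of this stands, and it is why the point is minor.

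A second defence is that the dropout rate is only approximate. This does not rescue the figure: even at 17% the need is 123, and 120 is enough only at 15% or less.

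A third is that the analysis section plans intention-to-treat and will explore multiple imputation, so a dyad missing at week 22 may still contribute earlier data. That may soften the loss, but the plan chose to enlarge the sample for dropout, and the enlargement as printed is not the one described.

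A reader might infer that the trial is underpowered or has to recruit 128. The article does not support either inference. It states no target power that 96 could miss, and 128 is needed only if both 102 and 20% must hold. Nor does it support reading the dropout allowance as 15%: the 20% is attributed to the prior study, and 15% appears nowhere.

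**Conclusion.** Wrong as written, and minor. The contradiction lies in the printed figures and needs no assumption: 102 and 20% give 128, while 120 and 20% give 96. No other section offers a different rate or a rule that explains 120. The shortfall is 6 dyads at the main endpoint, 5.9% of 102.

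The consequence for power does rest on assumptions that are not the protocol's: alpha 0.05, an interaction test, and three or four visits. On those, about 2 points of mean power are lost. The four-visit figures also apply the 22-week count through week 58, for which the article gives no dropout rate. The slip does not threaten the design or the choice of endpoint or analysis.

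**What to change.** Keep 120 dyads and keep the 20% assumption, which has a source. Replace the last sentence of the sample size section with a statement along these lines: *120 dyads will be recruited, 40 per site; with about 20% dropout, about 96 are expected to be evaluable at 22 weeks, which is below the scenario average of 102.* Add the power or the detectable effect at 96, and name the alpha, test and number of measurements used, so that the figure can be checked.

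Do not repair the sentence by changing the dropout rate to 15%; that would replace a sourced assumption with one chosen to fit the total. If the sponsor wants to retain both 102 and 20%, the recruitment figure is 128, or 129 with equal site numbers, but the size of the shortfall does not call for it.

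The cost is one rewritten sentence and a slightly less favourable stated figure. Recruitment, site quotas and analysis stay as they are.

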### Quantitative data analysis of primary and secondary outcome measures

Data will be entered by raters into SPSS statistics data editor (IBM SPSS Statistics) immediately after each evaluation session to decrease the likelihood of missing data. The use of multiple imputation will be explored to deal with any missing data, especially if a participant is unable to be assessed at one of the data collection time-points [48].

To ensure baseline similarity between groups, the experimental and control groups will be compared on socio-demographic and clinical variables with the use of *t*-tests for continuous data and Chi-square for nominal data. Descriptive statistics and histograms will be used to display differences between the groups. A repeated measures analysis of variance will be conducted to analyze dependent variable data, using a Greenhouse-Geisser correction to address issues with sphericity.

Scores for the primary outcome measures (SMAF and CATOM, items 1–14) will be compared between treatment groups over time using an intention-to-treat analysis. Intention-to-treat analysis dictates that all participants are included in the group to which they were allocated for purposes of analysis, whether or not they completed the intervention for that group. The same analysis will be applied to secondary outcome measures, which include the RNLI, CATOM (items 15–18), CBI, self-report FIM and hours of care provided by family caregivers. These secondary outcome analyses will be considered exploratory in view of the increased likelihood of Type I errors resulting from multiple statistical comparisons. Sensitivity analyses will be performed to compare the effect of the interventions on 1) caregiving spouses versus caregiving adult children, and 2) on participants receiving services at the different sites.

To test for changes in family caregiver burden due to the intervention, changes in older adults’ SMAF scores will be correlated with changes in their caregivers’ CATOM scores, using either a Pearson or Spearman correlation depending on the distribution of the data.

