### Randomization and blinding

Study coordinators at each site will randomly assign participants into the experimental group or control group immediately following their recruitment. The experimental group will consist of dyads that receive the home-based AT Provision, Updating and Tune-Up (ATPUT) intervention. Control group dyads will receive the customary care prevailing at the site where they were recruited. Centralized randomization software will be used to obtain the same number of participants in each group (www.randomization.com). Participating dyads will be blinded regarding their group assignment to the extent that they will be unfamiliar with the intervention received by the other group. Raters administering the outcome measures will be blinded until completion of the trial. Owing to the nature of the intervention, however, it is unfeasible to blind the study coordinators or the occupational therapists providing the intervention.

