The primary outcome measure for caregivers will be the Caregiver AT Outcome Measure (CATOM) [31, 41]. Construction of the CATOM was based on a conceptual framework of AT outcomes for AT users and their caregivers [30]. The first part (items 1–14) classifies specific activities for which the caregiver provides support, and then measures the frequency of caregiving and the perceived burden associated with the activities (e.g., feeling physically tired after helping with the specified activities). The original CATOM was designed to measure outcomes produced by AT interventions for a single problematic activity, whereas the current study will use a revised version that permits tracking the effects of AT interventions for multiple problematic activities. In the original study, the internal consistency of the activity-specific section of the CATOM was *α* = .73 [31]. The second part of the CATOM measures overall burden and will be used as a secondary outcome measure. The overall burden section is comprised of four items (15–18) measuring the caregiver’s degree of burden associated with all of the assistance provided (e.g., feeling that caregiving duties limits recreational and leisure activities). The internal consistency of this section was *α* = .78 [31]. Other secondary outcomes for caregivers will include hours of weekly care provided, the Caregiver Burden Inventory (CBI) [42], and the European Quality of Life (EQ-5D) visual analog system and descriptive system [43]. The EQ-5D measures the caregivers’ health status; the descriptive system is comprised of 5 items scored from 1 to 3, with higher total scores indicating worse health. The CBI provides a comparative measure of general caregiver burden whereas the CATOM focuses on caregiving as it relates to AT.

Socio-demographic and clinical data will be collected about older adults’ age, sex, level of education, ethnic origin, language, marital status, type of dwelling, diagnoses, duration of functional problems, and amount of formal caregiving received, if applicable. For family caregivers, collected data will include age, sex, level of education, language, the relationship with the older adult and cohabitation (yes/no), employment (yes/no), and duration of assistance.

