## Discussion

As a society, we need all the empirical, methodological, and theoretical knowledge available to respond adequately to the problems faced by older adults, their family caregivers, and service providers with respect to the efficient use of assistive technology. This study will be the first parallel-group RCT to examine an AT intervention with emphasis on both the older adult with disabilities and his/her family caregiver. Providing evidence of the effectiveness of such an approach will encourage service providers and clinicians to move forward with AT recommendations that are more attuned to the needs of both members of the dyad. It is important to recognize the societal importance of responding to the needs of family caregivers who in many instances may be aging themselves. Resource limitations and social policies that promote aging in place also bolster the call for an adequate response to family caregivers’ needs. Positive findings will highlight the value of an approach to AT provision that is more inclusive of family caregivers and will set the stage for econometric studies assessing its cost-effectiveness.

The study is designed to evaluate the effectiveness of an AT intervention in real-life conditions. As such, the results are prone to be influenced by a host of factors including older adults’ and family caregivers’ clinical and socio-demographic characteristics, their home-related problematic activities, their home environment, the device types they are supplied, and the dynamics of the relationship between them. This places a premium on having sufficient power to control for the concomitant effects of those factors. However, this study has the advantage of being built on the results of a previous one, which did detect a clinically significant effect of the ATPUT intervention [31]. Moving from that study to this planned, parallel-group RCT is a logical step toward the next best evidence. The results from the planned study should be transferable and usable in real life.

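### Baseline t-tests and chi-square tests cannot ensure that the randomised arms are similar; describe baseline instead and adjust for a short covariate list fixed in advance

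*Protocol article*

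**What the plan says.** The section on quantitative analysis of primary and secondary outcome measures gives both a purpose and a tool: "To ensure baseline similarity between groups, the experimental and control groups will be compared on socio-demographic and clinical variables with the use of *t*-tests". That tool serves the continuous variables; nominal ones are to be compared by chi-square. The section adds a display: "Descriptive statistics and histograms will be used to display differences between the groups". It states no significance level, no margin and no consequence of either result. The outcome model that follows is a repeated measures ANOVA with a Greenhouse-Geisser correction; no covariate is named. Caregiver relationship (spouse or adult child) and site appear in sensitivity analyses that compare the effect between those categories.

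The variables are set out under Quantitative measurements: "Socio-demographic and clinical data will be collected about older adults’ age, sex, level of education, ethnic origin, language, marital status, type of dwelling, diagnoses", followed by further older-adult items and a caregiver list. The Discussion expects clinical and socio-demographic characteristics and the dyad relationship, among other factors, to influence the results, and comments: "This places a premium on having sufficient power to control for the concomitant effects of those factors".

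**The concern.** The stated aim is an equivalence-type conclusion, and a test of difference cannot deliver it. If allocation is sound, every baseline difference is due to chance, so the null hypothesis is true before the test is run. The p-value also says nothing about whether an imbalance matters for the SMAF or the CATOM. That depends on how strongly the variable predicts the outcome.

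The check can mislead in both directions. A sizeable imbalance in a prognostic variable can be non-significant and draw no attention, and a trivial one can reach significance and invite adjustment chosen after seeing the data. Meanwhile the model, as written, makes no use of the prognostic variables that the Discussion singles out. At stake are bias conditional on the imbalance that happens to arise, and precision.

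**Working it through.** **Inputs.** Recruitment: "a sample of 120 dyads will be recruited (40 from each site" (Quantitative sample size). Allocation: "to obtain the same number of participants in each group" (Randomization and blinding), so 120/2 = 60 dyads per arm. Design values: "effect size (0.13 to 0.15), 2) correlations among repeated measures" of 0.5 to 0.6. Cohen's F came from a Cohen's D that "was calculated using standard deviations from our prior study [31] and then transformed into" F; the SDs are not given. The significance level is not stated; two-sided 0.05 is assumed throughout. The article gives no figure of its own for the baseline comparison, so there is none to reproduce.

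**1. What the t-test lets through.** Largest non-significant standardised difference = t(0.975, 118) × √(2/60) = 0.36 SD.

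**2. What the chi-square test lets through.** For a binary factor near 50%, 25/60 against 35/60 (a gap of 16.7 points) gives p = 0.068 (Pearson, no continuity correction). A split of 24/60 against 36/60 gives p = 0.028.

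**3. What it flags by chance.** The article lists 10 older-adult items, the MoCA and 8 caregiver items: 19 variables. Expected significant results under sound randomisation: 19 × 0.05 = 0.95. The chance of at least one is 1 − 0.95^19 = 62% if the variables are independent. They are not fully so (marital status, relationship and cohabitation overlap), so the 62% is only a guide.

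**4. Shift in the estimate (illustration).** Suppose one covariate has an observed imbalance of 0.35 SD, just under the limit in step 1, and correlation r with the change score (r assumed). Shift = r × 0.35:
- r = 0.5: 0.175 SD (simulated 0.174)
- r = 0.3: 0.105 SD (simulated 0.104)

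**5. Size against the design effect.** The shift is in SDs of change, so the design effect must be too. Assume the sample size rests on a within-between interaction with two visits, for which λ = F² × N × 2/(1 − ρ). A two-arm comparison of change scores has λ = d² × N/4. Equating them, d = 2F × √(2/(1 − ρ)):
- F = 0.13, ρ = 0.5: 0.26 × 2.00 = 0.52
- F = 0.15, ρ = 0.6: 0.30 × 2.24 = 0.67

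At r = 0.5 the shift is 0.174/0.67 = 26% to 0.174/0.52 = 33% of the effect. At r = 0.3 it is 0.104/0.67 = 16% to 0.104/0.52 = 20%.

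**6. Conditional error rate.** In 4,000 simulated trials with no treatment effect and the imbalance held at 0.35 SD, rejection was 12.9% unadjusted and 5.5% adjusted at r = 0.5, and 7.4% and 4.8% at r = 0.3. Averaged over all randomisations, the unadjusted test stays at 5%.

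**7. Precision.** Adjustment removes a share r² of the variance of the change score: 25% at r = 0.5 and 9% at r = 0.3.

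**The case against.** The strongest reply is that this is one loosely worded sentence. No rule says that p > 0.05 counts as similar, nothing is done with the result, and a descriptive display is planned as well. A covariate list is something an article commonly leaves to an analysis plan, and the Discussion signals an intent to control for such factors. All of that stands. What remains is that the article assigns the tests a purpose they cannot serve, and no later document makes that sentence right.

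A reader might infer four stronger things that the document does not support:

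- **That imbalances will be passed as similar and deliberately left unadjusted.** No pass rule is written, and the article does not exclude covariates. Nor is the test the only handling of these variables, since relationship and site also enter sensitivity comparisons, though these are not covariate adjustment.
- **That the trial's type I error is inflated.** The figures of about 13% and 7% are conditional on an observed imbalance that a given covariate shows, between 0.35 and 0.36 SD in size, only about 0.8% of the time. The unconditional rate is 5%.
- **That the shift is about 60% of the design effect.** This comes from setting d = 2F = 0.26 to 0.30 and treating that as an effect on the change score. An effect of that size on the analysed score would need roughly 350 to 470 dyads for 80% power, which does not fit the 102 stated. On the change scale the share is about half as large.
- **That the low power of these tests to detect a true baseline difference is the problem.** Under sound randomisation there is no true difference to miss. The relevant quantity is the observed difference.

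**Conclusion.** The concern holds in limited form. The tests cannot ensure similarity: observed differences up to 0.36 SD are non-significant at 60 per arm, and about one chance finding is expected among 19 variables. The consequence is conditional bias and lost precision, not an invalid primary test. In the illustration the shift is 0.17 SD (26–33% of the design effect) at correlation 0.5, or 0.10 SD (16–20%) at 0.3.

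These sizes rest on a two-sided 5% level, an imbalance close to the limit, assumed covariate correlations with change, and the two-visit interaction reading of F. The article does not say how many visits the sample size used. A covariate related equally to all visits would not bias a group-by-time test at all, so the shift applies only to variables that predict change.

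**What to change.** Replace the sentence on ensuring similarity with text such as: Baseline characteristics will be described by group, with standardised differences and without significance tests, and no statement of similarity will be based on p-values. Irrespective of observed imbalance, the primary analyses of the SMAF sub-scales and of CATOM items 1–14 will adjust for a short list of prognostic variables fixed before unblinding.

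The list is for the investigators to settle. Candidates already collected are the older adult's age and MoCA score for the SMAF, and caregiver relationship and cohabitation for the CATOM. The article does not itself identify these as the strongest predictors. If the group-by-time effect is the test of interest, include covariate-by-time terms, since a main effect alone does not address a covariate that predicts change.

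The cost is a change of wording, a few degrees of freedom per model and the need to fix the list in advance. No new data are needed.

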### Quantitative measurements

Table 2 highlights the measures to be administered at each time point. Raters will administer all quantitative measures. They will be trained by the study coordinator to ensure standardized administration of the measures. The primary outcome measure for care recipients will be a composite score from two sub-scales of the Functional Autonomy Measurement System (SMAF) [36]. These sub-scales will include self-care and mobility, and exclude the communication and mental functioning sub-scales that are unlikely to be affected by the ATPUT intervention. The SMAF will be administered to care recipients and caregivers together, but all other outcome measures will be administered to them separately. The secondary outcomes will be the self-administered Functional Independence Measure (FIM), a measure of self-assessed independence in daily activities [37, 38], and the Reintegration to Normal Living Index (RNLI), a measure of social participation that address daily activities, roles and relationships [39, 40]. Finally, the SMAF sub-scale relating to instrumental activities of daily living will also be used as a secondary outcome.

**Table 2 Tab2:** Quantitative measures and assessments collected at baseline, week 6, week 22 and week 58

Measures	Tools/Metrics	Baseline	6 weeks	22 weeks	58 weeks
Primary outcomes for AT users	SMAF sub-scales, self-care & mobility	X	X	X	X
Secondary outcomes for AT users	Self-report FIM RNLI EQ-5D SMAF sub-scale, IADL	X	X	X	X
Primary outcomes for family caregivers	CATOM (items 1–14)	X	X	X	X
Secondary outcomes for family caregivers	CATOM (items 15–18) CBI Hours of care	X	X	X	X
Socio-demographic and clinical data for AT users	MoCA^a^ Study-specific questionnaire	X			
Socio-demographic and clinical data for family caregivers	Study-specific questionnaire	X	X	X	X
Treatment fidelity and Intervention information	Adherence Form Life Changes Form Chart review^b^ Therapist survey^b^		X	X	X

*Abbreviations*: *CATOM* Caregiver Assistive Technology Outcome Measurement, *CBI* Caregiver Burden Inventory, *EQ-5D* European Quality of Life, *FIM* Functional Independence Measure, *IADL* Instrumental activity of daily living, *MoCA* Montreal Cognitive Assessment, *RNLI* Reintegration to Normal Living Index, *SMAF* Functional Autonomy Measurement System

^a^MoCA is only re-administered at T1, T2, and T3 if major changes are observed by the raters

^b^Chart reviews and therapist surveys are done at 6 weeks or later

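### Week 22 is named as the main endpoint, but the only stated primary analysis is an omnibus repeated-measures comparison over time with no week-22 contrast

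*Protocol article*

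**What the plan says.** The endpoint is fixed in two places of the protocol article.

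- Quantitative study design: "The measures will be re-administered to both groups 6 weeks, 22 weeks (the main trial endpoint), and 58 weeks after baseline evaluation".
- Quantitative sample size: "Sample size was calculated for the primary endpoint (22 weeks) for older adults and family caregivers separately".

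The analysis is fixed in Quantitative data analysis of primary and secondary outcome measures: "A repeated measures analysis of variance will be conducted to analyze dependent variable data", with a Greenhouse-Geisser correction for non-sphericity. For SMAF and CATOM items 1–14, the scores "will be compared between treatment groups over time using an intention-to-treat analysis". That section does not list the visits in the model, the model term that decides the result, a contrast at week 22, or a baseline covariate.

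Table 2 lists the "Quantitative measures and assessments collected at baseline, week 6, week 22 and week 58", and both primary outcomes are measured at all four visits. The sample-size section uses Cohen's f of 0.13 to 0.15, correlations of 0.5 to 0.6 that include the pre-post correlation, and sphericity values of 0.6 to 0.9.

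**The concern.** A test of whether two profiles differ over time is not a test of whether the arms differ at week 22. The group-by-time F test responds to divergence at any visit in the model. An early effect that has gone by week 22 is credible here. The article expects the interventions to be complete at about six weeks (Quantitative measurements) and describes discontinued device use as a known problem (Background). The trial could then be reported as positive on its main endpoint with no difference at that endpoint.

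The group main effect is no substitute. If baseline is a level, it averages in a visit at which randomisation implies no difference.

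There is also a cost in precision. The baseline score is already collected, but the stated analysis does not use it as a covariate for the week-22 comparison.

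**Working it through.** **1. The plan's own figure.** The article reports an average of 102 dyads before dropout. It gives no alpha, power or number of measurements, so the figure cannot be reproduced uniquely. I took alpha 0.05, f 0.13/0.14/0.15, correlation 0.5/0.6 and epsilon 0.6 to 0.9.

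- Group-by-time interaction, λ = f²·N·m·ε/(1−ρ), four measurements: mean N is 80.9 (power 0.80), 91.1 (0.85), 105.0 (0.90) or 127.2 (0.95).
- The same with three measurements: 95.0 (0.80) or 107.8 (0.85).
- Between-groups test, λ = f²·N·m/(1+(m−1)ρ): 271 or more.

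So 102 is plausible for an omnibus interaction and not for a between-groups test. This is plausibility, not proof.

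**2. Levels of the time factor.** A sphericity correction has meaning only with three or more levels. Table 2 and the pre-post correlation imply that baseline is one of them. Both four levels (baseline, 6, 22, 58 weeks) and three (baseline, 6, 22 weeks) are open, so both are checked.

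**3. Effect at week 6 only, none at week 22.** Inputs: n = 120 × 0.80 = 96, ρ = 0.55 (midpoint of the article's range), SD 1, alpha 0.05, compound symmetry. The noncentrality is λ = (n/4)·Σ(δₜ − δ̄)²/(1−ρ).

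- Four levels: Σ = 0.75δ², so λ = 24 × 0.75δ²/0.45 = 40δ², with df 3 and 282.
- Three levels: Σ = (2/3)δ², so λ = 24 × (2/3)δ²/0.45 = 35.6δ², with df 2 and 188.

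| δ (SD) | λ, four levels | Rejects | λ, three levels | Rejects | Week-22 test |
|---|---|---|---|---|---|
| 0.26 | 2.70 | 25% | 2.40 | 26% | 5% |
| 0.30 | 3.60 | 32% | 3.20 | 34% | 5% |
| 0.50 | 10.0 | 75% | 8.89 | 76% | 5% |
| 0.60 | 14.4 | 90% | 12.8 | 90% | 5% |

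The first two rows are the planned f of 0.13 to 0.15 under f = d/2: 2 × 0.13 = 0.26 and 2 × 0.15 = 0.30.

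**4. Power when week 22 does differ (0.5 SD, same inputs, four levels).** The noncentrality of week-22 ANCOVA is 0.5/√(4(1−0.55²)/96) = 0.5/0.1705 = 2.93, which gives 83%.

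- Effect sustained over all follow-ups: omnibus λ = 40 × 0.25 = 10.0, power about 75%.
- Effect at weeks 6 and 22 that is gone by week 58: Σ = δ², λ = 24 × 0.25/0.45 = 13.3, power about 87%.

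**5. Precision at week 22.** The variance factor is 2(1−ρ) for change from baseline and 1−ρ² for baseline adjustment.

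- ρ = 0.5: 1.00 and 0.75, ratio 0.75.
- ρ = 0.6: 0.80 and 0.64, ratio 0.80.

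The ratio is (1−ρ²)/(2(1−ρ)) = (1+ρ)/2.

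**The case against.** The strongest reply is that this is a condensed article. Model terms and follow-up contrasts are often set in an analysis plan, and nothing in the article forbids a week-22 contrast within the repeated-measures model. A reader might infer that the plan excludes such a contrast; it does not. But the article itself chooses the test, its correction and its comparison, and sizes the trial on repeated-measures inputs. What it does fix does not match its endpoint.

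A second reply is that the hypotheses speak of outcomes after the intervention, not of week 22. That is true, and a comparison over time bears on them. It does not displace an endpoint that is stated twice.

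Four stronger readings are tempting, and the documents do not support them.

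- That the model certainly has four levels and a 3-df test. This is an inference. With baseline, 6 and 22 weeks only, a spurious result from a week-58-only effect cannot arise, while the week-6 problem remains.
- That false signals near 90% are to be expected. That needs an effect of 0.6 SD, about twice what the planned f implies if f = d/2.
- That the omnibus test always dilutes a week-22 effect. It has more power than week-22 ANCOVA when the effect fades by week 58.
- That leaving baseline as a level, or comparing sites only in a sensitivity analysis, is an error. Repeated-measures ANOVA that includes baseline is valid in a randomised trial. Baseline adjustment and a site term are matters of precision.

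**Conclusion.** The mismatch between endpoint and analysis stands. As written, a significant primary result would not establish a difference at week 22, and the article names no quantity that would.

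For an effect confined to week 6, the group-by-time test rejects in about a quarter to a third of trials at the effect size that the plan appears to assume, and in 75% to 90% at 0.5 to 0.6 SD, against 5% for a week-22 test. The three- and four-level readings give nearly the same rates. For a sustained 0.5 SD effect, the loss of power against week-22 ANCOVA is about 8 percentage points (75% against 83%). The order reverses if the effect fades by week 58 (87% against 83%).

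These figures rest on assumed alpha 0.05, 96 completers, correlation 0.55, compound symmetry and, for the smallest effects, f = d/2. The article itself plans for some departure from sphericity. The variance ratio of 0.75 to 0.80 needs only equal variances at the two visits and the article's correlations. It compares baseline adjustment with the change contrast, not with the omnibus F.

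**What to change.** For SMAF (self-care and mobility) and for CATOM items 1–14, name one primary test each: the baseline-adjusted arm difference at week 22 with its 95% CI. Take it from a linear mixed model on the post-baseline visits, with arm by visit, baseline score by visit and an unstructured within-person covariance. Site may be added as a fixed effect for precision. Report weeks 6 and 58 as secondary contrasts of the same model.

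Restate the sample-size justification for that contrast, and state the standardised difference behind Cohen's f. This is not a formality. With 96 dyads and correlation 0.55, the noncentrality is 0.26/0.1705 = 1.53 to 0.30/0.1705 = 1.76, so power is about 33% to 41% if f = d/2, against 83% at 0.5 SD.

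The cost is a change to the analysis and sample-size text, recorded through the trial registry as the article already provides. No new data are needed. Effects at weeks 6 and 58 become secondary, and some power is lost if the effect fades by week 58.
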